## Abstract

**Background:**

High dietary quality can protect against diet-related chronic diseases. In the United States, racial and ethnic minorities and those with lower incomes consistently exhibit lower dietary quality. Independently-owned restaurants are a common prepared food source in minority low-income communities, but there are significant knowledge gaps on how to work with these restaurants to offer healthy food, due to underlying and dynamic complexities associated with providing healthy food options.

**Methods:**

The *Focus on Restaurant Engagement to Strengthen Health* (FRESH) study addresses this complex problem by leveraging systems science approaches to work with independently-owned restaurants. FRESH has two interrelated objectives: (1) to test impact on regular customer dietary quality via a multisite cluster randomized controlled trial in two low-income urban areas (Baltimore and the Washington DC metropolitan area), and (2) to use systems science approaches to develop, parameterize, and calibrate a simulation model. The intervention is theory-and practice-based, comprising three phases: restaurant engagement, low-sugar beverages and healthy meals. The FRESH intervention will be implemented for 12 months in a total of 24 intervention and 24 comparison restaurants. The study is powered to detect a 5-point change in the Healthy Eating Index (HEI) score of regular customers, which would signify a meaningful shift toward healthier eating patterns.

**Discussion:**

The FRESH study will test a novel, multilevel, multisite intervention that aims to improve access to healthier prepared food options among small, independently-owned restaurants located in under-resourced settings. The design of the FRESH intervention and its evaluation are described, as well as plans for the development of a system dynamics simulation model for policymakers and other stakeholders to virtually test future restaurant-based interventions.

**Clinical trial registration:**

https://clinicaltrials.gov, identifier, NCT05869149.

## Background

High dietary quality is a known protective factor against diet-related chronic diseases and all-cause mortality. For example, people with the highest dietary quality exhibit a 23% decreased risk of all-cause mortality compared to those with the lowest dietary quality (1). In the United States, non-Hispanic Black, Latinx, and other populations marginalized by inadequate policies bear an inequitable burden of chronic disease morbidity and mortality related to diet quality (2–4). Previous work to improve dietary quality sustainably has mainly focused on increasing access to healthful foods in retail store settings (5, 6). However, Americans spend about half of their food budget eating out (7, 8), representing at least a 15-fold inflation-adjusted increase since 1970 (9). This trend has contributed an additional 570 kcals to average daily energy intake, owing to both the increased frequency of eating out and larger portion sizes (10). Of the food consumed away from home, 76.8% is purchased at restaurants and fast-food establishments (11). Low-income and minority communities in urban settings are highly exposed to small, independently-owned prepared food sources in particular, most of which predominantly offer energy-dense, nutrient-poor options with few healthier options (12–14). These population groups spend a larger percentage of their food budget at these establishments (12), which are also not subject to policy efforts, such as menu-labeling (15). Working with independently-owned restaurants offers a unique venue to reach customers in low-income minority urban neighborhoods who may benefit most from improved dietary quality. Despite their prevalence in these under-resourced communities, little effort has been directed toward enhancing dietary quality in these establishments (11).

Improving access to and promotion of healthful foods in restaurants presents an inherently multilevel and potentially contradictory problem. Engagement in such efforts is affected by owners’ perceptions of customer demand for these foods, concerns with impact on revenues (e.g., ‘will offering healthy foods to my customers negatively affect sales?’), views concerning community health, and food sourcing challenges (16, 17). Our previous work (18–24) has demonstrated that it is feasible to promote existing healthful food options within independently-owned restaurants, improve their food preparation methods (5), and increase knowledge and acceptability of promoted healthful foods among customers (18, 21). However, community-based interventions tend to be resource-intensive and unsustainable if they do not consider the dynamic complexity across multiple levels of the food system.

The *Focus on Restaurant Engagement to Strengthen Health* (FRESH) study leverages systems science approaches to generate solutions to improve the food environment (25). Systems science addresses complex problems by understanding, identifying, and modeling multiple interacting factors—permitting the virtual testing of potential effects on dietary quality outcomes (26, 27), and saving resources that may otherwise be expended in trial and error (28). As an integral part of FRESH, systems science will inform the development of the trial, and resulting data from the trial will be used to parameterize and calibrate a system dynamics model that can predict the effects of similar strategies in other settings.

Therefore, this manuscript presents the protocol for the two inter-related objectives of this novel study: (1) to refine, implement and test—via a multisite randomized, controlled trial—the impact of the FRESH intervention in independently-owned restaurants located in two largely low-income minority urban sites, and (2) to develop, parameterize, and calibrate a simulation model using data generated from the trial.

## Methods and design

The FRESH study is innovative in its combination of community-based interventions and systems science—the intervention trial will inform the systems science approaches used (Figure 1). As depicted in the Figure, the two main study objectives will be achieved across four phases. First, comprehensive formative work, including community-based systems science group model building workshops was and will continue to be conducted to refine intervention strategies and develop an initial causal loop diagram. The impact of FRESH will be evaluated via multisite group-randomized controlled trial (RCT) design in two sites—Baltimore, Maryland, and the greater Washington DC metropolitan (DC metro) area—where neighborhoods will be randomly assigned to intervention or comparison conditions. Second, baseline data collected on neighborhoods, restaurants, and their customers will be used to parameterize the initial simulation model and guide the implementation of the intervention. Third, process and impact data from the implementation of FRESH will be used to further calibrate the simulation model. Finally, an interactive, web-based, user-friendly dashboard (29) will be disseminated to policymakers allowing them to apply the system dynamics model to other urban settings.

**Figure 1 fig1:**
[figure not shown]
Integration of FRESH intervention study phases with the systems dynamic model.

### Formative and participatory research approaches

The FRESH study leans on academic-community expertise and partnerships with particular experience working with family-style, independent, Latinx-owned restaurants in the DC metro area and in Baltimore (18). This includes leveraging active Community Advisory Boards (CABs) per each site, and using community data collectors and interventionists who are knowledgeable and have deep lived experiences in the communities and neighborhoods in question.

In addition, the FRESH study utilizes extensive formative work to contextualize the trial’s intervention strategies for each site based on qualitative data from: (1) in-depth interviews with restaurant owners/managers and restaurant suppliers (*n* = 31), and (2) structured back-and front-of-house (*n* = 27) and back-of-house observations (*n* = 17).

#### In-depth interviews with restaurant owners/managers

Semi-structured interviews were conducted with the owners/managers of independently-owned restaurants located within predominantly low-income neighborhoods selected at each site. The interview guide was designed to deepen and contextualize our understanding of the restaurants’ and owners’ business history (e.g., length of time in business), business practices (e.g., processes related to suppliers, procurement, delivery, cooking settings, level of training of cooks and willingness to innovate, client-facing staff schedule, restaurant layout), reasons for offering the foods and beverages they do, perceptions of their customers’ reactions toward potential menu changes, and types of promotions they have tested and found to be more or less /successful with their customers.

#### Structured back-of-house observations

Direct observations were carried out in the kitchen or ‘back-of-house’ area (e.g., common areas where foods are prepared, and customers are not allowed). The observation protocol for the back-of-house was designed by the research team for the purpose of this intervention and will capture the number of kitchen staff, cooking equipment, cooking storage, cooking tools, cooking practices as observed (e.g., recipes, types of oil) and availability of specific food groups (e.g., whole grains, fruits without added sugars, vegetables).

#### Structured front-of-house observations

For the ‘front-of-house’, or customer area, observations, we used the NEMS-R (Nutrition Environment Measures Survey-Restaurants) tool (30). This instrument assesses facilitators and barriers to healthy eating, including the restaurants’ promotion of healthful foods that are available on the menu as well as nutrition information, portion options, and other promotional materials.

### Group model-building workshops

Following completion of the formative research, we will conduct a series of group model-building workshops. Group model-building is a participatory approach that elicits participants’ insights into how the restaurants’ systems currently work (including supply procurement, food preparation, service, and interactions with customers), identifying feedback loops to maximize demand, profitability, and healthfulness (31, 32). The first step of the group model building process will be to revise and expand the original causal loop diagram (Figure 2) based on our research team’s experience conducting the formative work—and to produce a revised version (version 2). We will then hold two group model building workshops, one in each research site, where participants will further refine the causal loop diagram (versions 3 and 4). There will be one causal loop diagram for both research sites.

**Figure 2 fig2:**
[figure not shown]
Early causal loop diagram of the restaurant food environment.

Group model building participants will engage in systems-thinking discussions about key factors that contribute to healthy food availability in restaurants, including the role of food access and procurement, food preparation, and the customer nutrition environment (e.g., the three core components of the FRESH intervention). They will add to and expand the existing CLD based on the formative research, CAB input and the experience of the FRESH team as we begin baseline data collection with restaurants and their owners.

### Site selection, recruitment and baseline data collection

#### Site selection

The study sites are two urban areas: Baltimore, Maryland, and the greater Washington DC metropolitan (DC metro) area. The latter comprises the adjacent urban areas of the District of Columbia, Prince George’s, and Montgomery Counties in Maryland. In total, both sites contain hundreds of restaurants in densely populated areas, including carryout-type restaurants, restaurants with seating/dining areas, and carryouts located in food markets (11).

In Baltimore, neighborhoods (as defined by clustered census tracts) will be selected if they are predominantly (>80%) African American and low-income (with >15% of the population below the poverty level). There are about 1.5 small, prepared food sources per 1,000 residents within city limits, and the majority are independently-owned, carryout-type restaurants (80%) in low-income neighborhoods (11, 33). These restaurants emphasize deep-fried and high-fat foods on their menus, including fried chicken, French fries, pizza, and submarine-style sandwiches.

In the DC metro area, neighborhoods will be selected from clustered census tracts that are both low-income (with >15% of the population below the poverty level) and have a significant Latino population (>35%). These tracts often house smaller neighborhoods that are predominantly (>80%) Latinx, mostly from El Salvador and Guatemala. There are 1.24 restaurants per 1,000 residents in the DC metro area, and many offer primarily Central American foods. These restaurants offer a combination of traditional foods from the owners’ home country, as well as newer dishes, high in saturated fat and sugary beverages.

#### Inclusion and exclusion criteria

Table 1 presents criteria for inclusion in and exclusion from the FRESH trial.

**Table 1 tab1:** Inclusion and exclusion criteria for the FRESH trial, by level.

Level	Inclusion	Exclusion
Neighborhood/ clustered census tract	Baltimore study area eligibility criteria: Predominantly (>80%) African American residents Having at least 8 independently-owned restaurants >15% of residents below poverty level DC metro area eligibility criteria: High (>35%) proportion of Latinx residents Having at least 8 independently-owned restaurants >15% of residents below poverty level	Does not meet inclusion criteria
Restaurants	Located within a designated study area (clustered census tract) In good standing with Health Department Inspections Independently-owned In operation for at least 3 years under the same ownership	Franchise of a national, regional, or state chain (e.g., Burger King, KFC, etc.) Very limited hours of operation (open <5 days a week, < 8 h/day) Specialty store (e.g., coffee shop, bakery, donut shop, etc.)
Customers	Adult (18+ years) Regular restaurant customer (buys food > = 1x/week) Live in a household of at least two persons Current resident of study neighborhood	Anticipate moving out of Baltimore or DC metropolitan area in the next 18 months Pregnant

#### Randomization of restaurants

Following completion of the baseline data collection, the 16 census tract clusters will be randomized to intervention or comparison, using a public community-engaged approach we have previously employed in a Native American community setting (34). Half of the restaurants (*n* = 24) will therefore receive the FRESH intervention. At the customer level, half of the customer sample (*n* = 288) will be regular consumers at restaurants receiving the FRESH intervention. The sampling design is presented in Figure 3.

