### Sample size and power

Our power calculations are based on the primary hypothesis, which involves testing the change in mean Healthy Eating Index (HEI) of customers between study groups. Our chosen effect measure is the standardized mean effect of the intervention, representing the difference in mean change in HEI score between the intervention and comparison groups. This measure is standardized by the total variability in the outcome, denoted as the standardized main effect (ES).

$$\begin{array}{l} \mathrm{The standardized main effect}\;\left(ES\right)\\ \;=\frac{\mu_{I}-\mu_{C}}{\sqrt{\tau_{\mathrm{restaurent}}+\tau_{\mathrm{neighborhoods}}+\sigma^{2}}} \end{array}$$

Here, μ_I-μ_C is the mean difference of intervention and comparison groups, respectively. *σ*^2 corresponds to within cluster variation, τ_restaurant corresponds to between restaurant variation within neighborhoods, and τ_neighborhoods corresponds to between neighborhood variation within a site. For our calculations, we assumed a difference in means of 5 points in HEI score would be meaningful, leading to μI − μC = 5. Using data from one of our prior multilevel intervention studies (48), we estimated the standard deviation of the change in HEI outcome to be 9–10 points, giving us σ^^2^ = 9.52^^2^ ≈ 90. We also assumed the variance of change in HEI score between restaurants within a neighborhood, and between neighborhoods within a site, would be small relative to the variance within a restaurant, therefore assuming τ_restaurant = τ_neighborhood≈5_._ Thus, we aimed to be powered to detect an effect size of ES = 0.5. This is equivalent to detecting a medium-sized effect.

Power calculations were conducted using the Optimal Design program (49) and following the documentation for “Multisite cluster randomized trials with treatment at level 3 randomization” section. For all calculations, we assumed a significance level of *α* = 0.05, an effect size of *δ* = 0.5, a total of L = 2 sites (for Baltimore and DC metro area), and an effect size variability of 0, corresponding to fixed effects by site rather than random effects by site.

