We varied the number of neighborhoods per site (*K* = 4 to 12), the number of restaurants per neighborhood (*J* = 2,3,4), and the number of customers per restaurant (*n* = 10 to 20). We varied the proportion of variability in the outcome explained by site (Baltimore vs. DC metro area) from 0 to 20% (*B* = 0, 0.1, 0.2). We varied the intra-class correlation coefficients for both the level 2 variable (restaurants) and the level 3 variable (neighborhoods) from 0.01 to 0.1 (ρπ = ρβ = 0.01, 0.05, 0.1). Finally, we assumed a loss to follow-up of 20%. Power is calculated as a function of the number of neighborhoods per site, the number of restaurants per neighborhood, and the number of participating customers per restaurant at initial and follow-up visits. If 8 neighborhoods are randomly assigned to intervention and comparison groups at each site (8 neighborhoods per arm total), the power to detect an effect size a difference of 5 HEI points will exceed 80% if we recruit at least 12 customers per restaurant (*N* = 576) when ICC = 0.05. These calculations account for a potential 20% loss to follow-up.

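### The randomization section does not state 4:4 allocation within each site, which the power calculation takes for granted; balancing on the baseline data already in hand would be a cheap addition

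*Protocol article*

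**What the plan says.** In the Protocol article, *Randomization of restaurants* sets out the allocation. It takes place "Following completion of the baseline data collection", and "the 16 census tract clusters will be randomized to intervention or comparison". The draw is to be made "using a public community-engaged approach we have previously employed in a Native American community setting". Half of the restaurants (24) and half of the customers (288) are to be in the intervention arm, so the overall split is 8:8. Site is not mentioned, and neither is any balance rule. The section refers to a figure for the sampling design, which is not available here, and to a cited source for the method.

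*Sample size and power* uses the design option "Multisite cluster randomized trials with treatment at level 3 randomization" with two sites and "an effect size variability of 0, corresponding to fixed effects by site rather than random effects by site". It claims power above 80% on the condition that "8 neighborhoods are randomly assigned to intervention and comparison groups at each site", with 8 neighborhoods per arm in total.

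*Data analysis* defines the primary model: change in HEI as outcome, fixed effects for intervention and site, random effects for restaurant and neighborhood. An intervention-by-site interaction is a secondary analysis. Customer, restaurant and neighborhood covariates, with income and restaurant density among the examples, are only to be considered. Baseline HEI is not named as a covariate.

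**The concern.** The section that fixes the allocation is less specific than the section that relies on it. An 8:8 split overall does not guarantee 4:4 in Baltimore and 4:4 in the DC metro area. The two sites differ by design in population and type of restaurant. The site term in the model removes bias from a site imbalance, but it does not restore the precision lost to an uneven split. The site-specific effects behind the interaction would also be estimated less well.

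The second matter is an opportunity. Only 16 units are allocated, once, and their baseline HEI and neighborhood characteristics will be known at that time. A change-score analysis without baseline HEI is sensitive to a chance difference in baseline diet quality, because the arm that starts higher tends to change less. Such an imbalance can be limited before the draw but not undone after it.

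**Working it through.** **Inputs.** From *Sample size and power*: difference 5 HEI points; variances of change 5 (neighborhood), 5 (restaurant) and 90 (within restaurant); alpha 0.05 (taken as two-sided, since the article does not say); ICC 0.05 at both levels; 2 sites with 8 neighborhoods each; 12 customers per restaurant; 20% loss. From the Discussion: 3 restaurants per neighborhood.

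**1. The plan's own figure.**
- Effect size = 5/√(5+5+90) = 0.50.
- Completers per restaurant = 12 × 0.8 = 9.6, so 3 × 9.6 = 28.8 per neighborhood.
- Variance of a neighborhood mean, with total variance 1: v = 0.05 + 0.05/3 + 0.90/28.8 = 0.0979.
- With 4:4 in each site, variance of the effect = 4v/16 = 0.0245, SE = 0.156, noncentrality = 0.50/0.156 = 3.20.
- Noncentral t power: 84.0% with 13 df (primary model), 83.5% with 12 df (interaction included).

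The claim of more than 80% reproduces.

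**2. What a pooled 8:8 draw would do.** Let *a* be the number of intervention clusters in one site. The probability of *a* is C(8,a)·C(8,8−a)/C(16,8), and C(16,8) = 12,870. With site in the model, the information for the treatment effect is 2·a(8−a)/8 and the variance is v divided by that information.

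| Split within site | Probability | Information | Power (13 df) |
|---|---|---|---|
| 4:4 | 4,900/12,870 = 38.1% | 4.00 | 84.0% |
| 5:3 | 6,272/12,870 = 48.7% | 3.75 | 81.6% |
| 6:2 | 1,568/12,870 = 12.2% | 3.00 | 72.5% |
| 7:1 | 128/12,870 = 1.0% | 1.75 | 49.9% |

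- 6:2 or worse: 13.2% of draws. This includes 8:0, with 2 draws in 12,870, where the site-adjusted effect cannot be estimated.
- Power averaged over draws: about 81% (81.1% with 13 df, 80.5% with 12 df). With 12 df, power at 6:2 is 72.0%.
- At 6:2, the variance of a site-specific effect is proportional to 1/6 + 1/2 = 0.667, against 1/4 + 1/4 = 0.5 at 4:4, an increase of one third.

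**3. Chance imbalance in baseline HEI under a 4:4 draw.** The article gives no variance for baseline HEI, so this step rests on an assumption. Take the planning variances for change, multiplied by k. The neighborhood mean of 36 customers has variance k(5 + 5/3 + 90/36) = 9.17k, and the arm difference has SD √(4 × 9.17k/16).

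| k | SD of arm difference (HEI points) | Chance of more than 2 points |
|---|---|---|
| 0.5 | 1.07 | 6% |
| 1 | 1.51 | 19% |
| 2 | 2.14 | 35% |

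**4. What a baseline difference does to the change score.** If follow-up HEI rises by *b* points per point of baseline, a baseline difference D shifts the contrast in change by (b−1)D. For D = 2 and b from 0.3 to 0.7 (assumed), the shift is 1.4 to 0.6 points against the arm that starts higher. This is 28% to 12% of the 5-point target.

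**5. What restriction would gain.** There are C(8,4)² = 70² = 4,900 site-stratified allocations. In simulation, keeping the best-balanced 10% (490) on mean baseline HEI plus two independent neighborhood covariates cut the SD of the arm difference at k = 1 from about 1.5 to about 0.5–0.7, with essentially no draws above 2 points. At k = 2 the restricted SD was about 0.8, against 2.14 unrestricted.

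**The case against.** A reader might infer that the trial plans a single draw from a pool of 16. The article does not support that. The randomization section gives the number of units without saying that they form one pool. The power section speaks of assignment at each site, and both the power model and the primary model carry site. These point to assignment within site. What remains is that the site-by-site wording is a condition of the power statement, gives only the total per arm, and is absent from the procedure itself.

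A reader might also infer that the lack of a balance rule is an error, or that balancing was considered and rejected. Neither follows. Site-stratified cluster randomization without covariate constraints is valid. Over repeated draws the change-score contrast is unbiased and its standard error already includes chance imbalance. The article condenses a fuller protocol and cites a source for its method, and it says nothing about restricted allocation either way.

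The size can be challenged too, and rightly. Even under a pooled draw, average power stays just above 80% and a 5:3 split keeps about 82%. The baseline figures borrow variances stated for change, and a baseline difference does not carry over one for one. Finally, covariate adjustment is already under consideration, although baseline HEI is not among the examples given.

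**Conclusion.** The site part holds as a mismatch to reconcile: the randomization section should state the 4:4 allocation within site that the power section assumes. It does not prove a faulty design. If allocation is stratified, nothing is lost and the power claim stands at about 84%. If it were pooled, average power would fall to about 81%, and about one draw in eight would leave 72–73% or less. These figures assume a two-sided test, ICC 0.05 at both levels, 3 restaurants per neighborhood and 9.6 completers per restaurant.

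The balance part is a worthwhile improvement, not a correction of an error. Its benefit depends on the unknown baseline variance: the SD of the arm difference in baseline HEI is about 1.1 to 2.1 points if the baseline variances are half to twice the planning values for change.

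**What to change.** 1. In *Randomization of restaurants*, state that allocation is stratified by site, with 4 intervention and 4 comparison clusters in each. This costs one clause.
2. Recommended: before the public event, list the 4,900 site-stratified allocations. Keep those within a pre-set limit on the arm difference in neighborhood mean baseline HEI and in one or two neighborhood covariates, such as poverty rate or restaurant density. Number them and draw one number in public, so that the community-engaged draw is kept. Choose the limit so that many allocations remain.
3. Include baseline HEI and the balancing covariates in the primary model. This uses the baseline information for precision and makes the analysis match the restricted allocation.
4. If the size of the likely imbalance is reported in support, show it over a range of baseline variances, or use the variance observed at baseline.

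The costs are a short script, a brief explanation at the event, and about one between-cluster degree of freedom for each neighborhood-level covariate, out of 13. The number of such covariates should therefore stay at one or two. All of this must be settled before the draw.
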